## 5.9 STUDY COMPLETION AND DISCONTINUATION

5.9.1 STUDY COMPLETION

The study is complete when the oral food challenge tests at 28 weeks of age are performed. When primary outcome evaluation is finished, study treatment for a participant is completed and study physicians observe, conduct tests, and evaluate the participant at the time of the study completion.

5.9.2 STUDY DISCONTINUATION

Participants can discontinue the study if they meet any of the criteria described below:

Study physicians determine that the participants are unable to continue study treatment in PACI study due to exacerbation of AD

Participation in the study is discontinued because of adverse events

Proxies (parents or legal guardians) withdrawal from the study

Participants are unable to attend a study visit because of moving or hospital transfer

Death during study participation

PACI study is terminated

Study physicians determine that it is difficult to continue the study intervention for participants for reasons other than the above

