5.1.3 ANTICIPATED PARTICIPANTS AND STUDY DURATION

Anticipated number of participants: N=650 (aggressive intervention group: n=325 and conventional treatment group: n=325)

Duration of the study registration: 2 years from the day of IRB approval

Duration of the study intervention: 3 years after IRB approval

The study duration will be from study entry until completion of primary outcome assessment or until study termination. During the study duration, study treatment is continued unless the study treatment discontinuance criteria are satisfied. The study duration will be postponed under IRB approval if the study is not completed as scheduled.

Justification for the anticipated number of participants

Palmer *et al.* performed a double-blind, randomized controlled trial for infants with AD to test whether or not one-sixth of a raw whole egg taken every day can prevent development of IgE-mediated egg allergy. The infants were allocated to receive 1 teaspoon of pasteurized raw whole egg powder (n=49) or rice powder (n=37) daily from 4 to 8 months of age (67). A high proportion (31% [15/49]) of infants randomized to receive egg had an allergic reaction to the egg powder and 20% (10/49) had a reaction at the first ingestion of egg powder (one-sixth of a raw whole egg) at 4 months of age. When the control group participants received half of a raw egg provocation test at 12 months, 51% (18/35) were diagnosed with IgE-mediated egg allergy. These data suggested that prevalence of egg allergy in infancy is likely to depend on the provocation dose of egg and the preparation of egg such as heated or raw, and also on age and race of the participant. Therefore, we estimate that at least 30% of the participants in the conventional treatment group in this study will be diagnosed with IgE-mediated hen’s egg allergy using an oral food challenge test at the age of 28 weeks. However, the prevalence of IgE-mediated hen’s egg allergy among infants treated with early aggressive intervention for AD has never been reported. In Japan, it is common that infants at the age of 28 weeks do not eat hen’s eggs, and the prevalence of hen’s egg allergy at the age of 28 weeks in Japan is unclear. We consider a clinically effective prevalence of infants with early aggressive intervention for AD to be 20%. As discussed above, the calculated sample size is 614. Taking into consideration that the rate of drop out is about 5%, we determined the anticipated number to be 650.

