# 9 STATISTICS

## 9.1 SAMPLE SIZE

For sample size calculation, the proportion of egg allergy in early aggressive intervention and conventional treatment groups are estimated to be 20% and 30%, respectively. With a one-sided significance level of 0.025, 581 participants are needed to provide 80% statistical power. One interim analysis examining efficacy and safety is planned when almost half the participants are finished their trial assessment. Considering the interim analysis, 614 participants are needed. We expect a drop of about 5%, and set the target number of study participants to 650.

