9.3.2 PRIMARY ENDPOINT ANALYSIS

Statistical analysis will be performed following the intention to treat (ITT) principle, where participants will be analyzed as they were randomized, not as they were treated. The primary analysis is performed using FAS, and secondarily using PPS. The participants who have missing data for the presence of IgE-mediated hen’s egg allergy are defined as having IgE-mediated hen’s egg allergy and included in the FAS analysis. The participants who have missing data for the presence of IgE-mediated hen’s egg allergy are excluded from the PPS analysis. To verify the study hypothesis, “the aggressive intervention group has lower prevalence of IgE-mediated hen’s egg allergy compared to the conventional treatment group”, the main comparison is the null hypothesis that the percentage of IgE-mediated hen’s egg allergy is higher in the aggressive treatment group than in the conventional group" and the alternative hypothesis is that the percentage of IgE-mediated hen’s egg allergy is lower in the aggressive treatment group than in the conventional group. The *p* value is calculated by the difference in percentage with a one-sided test. The significance level is 0.025. The difference and ratio of these proportions and their 95% confidence intervals for each intervention group will also be calculated.

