9.3.4 INTERIM ANALYSIS

Interim analysis is conducted with the aim of preventing disadvantages to participants due to excessive efficacy and safety procedures unintended in study treatment. The interim analysis is performed when almost half of the participants finish their assessments for the primary endpoint. The interim analysis is done for primary endpoint and safety endpoints. The study registration for study participants does not stop while conducting the interim analysis. The analysis of primary endpoint is performed along with 9.3.2 primary endpoints analysis. The stopping boundary for the analysis of primary endpoint will be calculated based on the O’Brien–Fleming type with a Lan–DeMets α and βspending function at the actual information time. For example, the significance levels of effective discontinuation and invalid discontinuation are 0.0015 and 0.2883, respectively, with the interim analysis for 307 participants who are half of the planned study participants. The interim analysis is conducted by a trial statistician of the interim analysis under a closed situation. The statistician prepares a report of interim analysis results and submits it to the independent data monitoring committee. The results of the interim analysis will be evaluated by the members of the independent data monitoring committee to investigate whether or not the study continues, and the investigation result report is submitted to the principle investigator.

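### After an early stop, the missing-equals-allergic rule in 9.3.2 would also cover infants not yet due for the egg challenge, diluting the reported FAS effect if their challenges are not completed

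*Protocol*

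**What the plan says.** Five parts of the protocol bear on this.

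- **9.3.2 (primary analysis).** Infants with no egg-allergy result "are defined as having IgE-mediated hen’s egg allergy and included in the FAS analysis". The rule makes no distinction by reason and does not mention infants who have not reached the challenge age. The PPS leaves missing outcomes out, but it is secondary.
- **9.2 (analysis sets).** The FAS drops only infants never treated, infants with no data after treatment start, and infants found ineligible. An infant with a week 2, 4 or 8 visit therefore stays in.
- **5.1.3 and 5.9.2 (end of participation).** "The study duration will be from study entry until completion of primary outcome assessment or until study termination". Section 5.9.2 lists "PACI study is terminated" as one criterion for discontinuation, in permissive wording.
- **9.3.4 (interim).** "The study registration for study participants does not stop while conducting the interim analysis". The example levels at 307 participants are 0.0015 for efficacy and 0.2883 for futility.
- **17.2 (stopping).** It foresees the purpose being achieved before recruitment ends, and leaves what happens to enrolled infants to the principal investigator's instruction.

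**The concern.** Counting a missing challenge as allergy is a conservative device for drop-outs, planned at about 5%. An infant who is ten or twenty weeks old when the trial ends is a different case: the result is absent because of the calendar, and its absence carries no information about allergy. Because enrolment runs on through the interim, any stop finds a group of infants in this position.

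Read literally, 9.3.2 adds one event for each of them, in roughly equal numbers per arm. That raises both prevalences and pulls the risk difference and risk ratio towards no effect. What is at stake is the published primary estimate after an early stop, in a trial whose protocol says (5.1.3) that egg-allergy prevalence at this age in Japan is not known.

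**Working it through.** **1. The plan's own figures.** Inputs from 9.1: proportions that "are estimated to be 20% and 30%, respectively", and "With a one-sided significance level of 0.025, 581 participants are needed to provide 80% statistical power". With unpooled variance, total N = 2 × (1.960 + 0.842)² × (0.30×0.70 + 0.20×0.80) / 0.10² = 580.8, so 581, as stated. Two looks at half information, with O'Brien–Fleming-type alpha and beta spending and non-binding futility, give an efficacy level of 0.00153, a futility level of 0.288 and an inflation of 1.056. Then 580.8 × 1.056 = 613.3, so 614: "Considering the interim analysis, 614 participants are needed". Next, 614/0.95 gives 647, rounded up in the plan: "We expect a drop of about 5%, and set the target number of study participants to 650". The design figures reproduce.

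**2. Infants waiting at a stop.** Entry at 7–13 weeks is days 42–90 and week 28 is days 189–195 in the age table of section 3. The wait is therefore 189 − 90 = 99 to 195 − 42 = 153 days, or 14.1 to 21.9 weeks (middle 18). Assumption: 650 infants accrue evenly over two years (104.36 weeks), or 6.23 a week.

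- All waiting infants: 6.23 × 14.1, 18 and 21.9 = 88, 112 and 136.
- Without those in their first two weeks, who may have no post-start data and so fall outside the FAS: 75, 100 and 124.

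I take 100, with a range of 75 to 136. As a share of the resulting FAS this is 100/407 = 25% (75/382 = 20% to 136/443 = 31%).

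**3. Effect on the estimate.** With n = 153.5 assessed per arm and m waiting per arm, each rate becomes (p×n + m)/(n + m), and the risk difference is multiplied by n/(n + m).

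With 30% in the conventional arm, the rate in the aggressive arm that gives one-sided p = 0.0015 (pooled z = 2.97) is 15.8%.

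| Waiting infants scored allergic | Conventional | Aggressive | Difference (points) | Risk ratio | One-sided p |
|---|---|---|---|---|---|
| 0 | 30.0% | 15.8% | 14.2 | 0.53 | 0.0015 |
| 75 | 43.7% | 32.3% | 11.4 | 0.74 | 0.011 |
| 100 | 47.2% | 36.5% | 10.7 | 0.77 | 0.014 |
| 136 | 51.5% | 41.6% | 9.9 | 0.81 | 0.019 |

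For the row of 100: (46.05 + 50)/203.5 = 47.2%, (24.21 + 50)/203.5 = 36.5%, and the multiplier is 153.5/203.5 = 0.754.

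If the trial ended for another reason with the planning rates observed (30% v 20%, difference 10.0, risk ratio 0.67), 100 waiting infants would give 47.2% v 39.7%, difference 7.5, risk ratio 0.84.

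**4. Two checks on the size.** If termination comes three months after the interim cut, about 81 more infants have been assessed (27.1 a month × 3), or 194 per arm. The boundary rates with 50 waiting per arm then give 44.3% v 33.0%, difference 11.3, risk ratio 0.74, p = 0.005. Separately, in the 307-infant case the diluted p reaches 0.025 only at about 97 waiting per arm (194 in all), beyond the range in step 2.

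**The case against.** The strongest reply is that the protocol does not make this happen. Section 5.9.2 permits discontinuation without requiring it, 5.9.1 defines completion by the challenge, and 17.2 leaves enrolled infants to later instruction. If the challenges go ahead, the problem disappears. This stands: a reader might infer that waiting infants are necessarily discontinued and scored allergic, and the text does not say so. But nothing requires the challenges either, so the primary estimate would turn on an instruction given once results are known.

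A second reply is that 9.3.4 runs the interim along the lines of 9.3.2 on about 307 assessed infants, so missing must mean due but not obtained. That is the sensible reading, but 9.3.2 does not state it.

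Third, the SAP, which is not at hand, may define the analysis after a stop. It may, but an exception there would depart from an unqualified rule in the protocol.

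Fourth, the waiting count is assumed, and 5.1.3 allows the study to be extended. If 650 took three years, the count would be 650/156.5 × 16 = 66 and the multiplier 153.5/186.5 = 0.82, for a difference of 11.7 points. The dilution would be smaller but still present.

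Finally, the PPS omits missing outcomes and the bias is towards no effect. Both are true, but neither corrects the primary FAS figures.

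**Conclusion.** The point holds as a conditional one. If the trial is terminated early and the outstanding challenges are not done, 9.3.2 as written counts about 100 infants (75 to 136) as allergic for a purely administrative reason. For a result on the efficacy boundary, the risk difference shrinks by about a quarter (20% to 31%), the risk ratio moves from 0.53 to about 0.77, and the prevalences rise by about 17 and 21 points. These figures rest on even accrual of 650 over 24 months, 307 assessed infants and an equal split of waiting infants between arms. At the planning rates, an efficacy stop at the interim has a probability of about 18%.

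Two stronger readings are not supported. A reader might infer that the interim decision is compromised or that significance is lost: the decision uses assessed infants, and p stays below 0.025 across the whole range. A reader might also extend the point to a single site closing: 5.9.2 names only termination of the trial, and the site-stop item in 17.2 sets no data rule.

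**What to change.** In 9.3.2, with a cross-reference in 9.3.4, state that:

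- scoring a missing result as allergy applies only to infants whose 28-week window (28 weeks plus the 14 days in 6.1) had closed without a challenge by the termination date;
- infants not yet due at termination are not imputed as allergic, and any 28-week result obtained, before or after the stop, is used as observed;
- infants never challenged for this administrative reason are left out of the primary FAS estimate, and the analysis that imputes all of them as allergic is reported as a sensitivity analysis.

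Reconcile 5.1.3, 5.9.2 and 17.2 on whether the 28-week outcome is still collected after termination. Whether study treatment continues in these infants is for the sponsor to settle.

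The cost is a few sentences and no extra infants, and nothing changes if the trial runs to completion. The downside is precision: if no post-stop challenges are obtained, the FAS after an early stop is smaller by about a quarter (100 of 407). If only some families return, those results come from a self-selected group whose parents know the allocation, which is a further reason to keep the sensitivity analysis.

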# 6 STUDY ASSESSMENTS (Observation, test, and evaluation)

## 6.1 ASSESSMENT SCHEDULE

|  | Study treatment start | Study period | | | |
| --- | --- | --- | --- | --- | --- |
| Visit | 1 | 2 | 3 | 4 | 5 |
| Study duration | Entry  (Day 0) | 2 weeks after entry  (Day 14) | 4 weeks after entry  (Day 28) | 8 weeks after entry  (Day 56) | 28 weeks of age |
| Visit windows |  | ±6 days | ±7 days | ±7 days | ±14 days |
| Informed consent | X |  |  |  |  |
| Background information | X |  |  |  |  |
| Nutrition | X | X | X | X | X |
| Living environment | X | X | X | X | X |
| Body height | X | X | X | X | X |
| Body weight | X | X | X | X | X |
| Oral food challenge test  (hen’s egg) |  |  |  |  | X |
| IgE-mediated FA  by interview | X | X | X | X | X |
| Wheeze | X | X | X | X | X |
| Total IgE, egg white, ovomucoid, milk, wheat soy, peanut, and Ara h2-specific IgE and IgG4 antibodies in serum | X |  |  |  | X |
| EASI  by blinded physician | X | X | X | X | X |
| POEM  by caregivers |  | ✔ | ✔ |  | Every week |
| Disease-free days of AD |  | X | X | X | X |
| Amount of emollients and TCSs including rescue medication usage |  | X | X | X | X |
| Days of applying emollients and TCSs including rescue medication usage |  |  |  | Daily |  |
| IDQoL and DFI scores | X | X | X | X | X |
| Salivary cortisol |  | X | X | X | X |
| Concomitant therapy | X | X | X | X | X |
| Adverse events |  | X | X | X | X |
| Amount of emollients and TCSs used |  | X | X | X | X |

Measurement of specific IgG4 antibody titer is carried out at the Institute of Enzyme Research, University of Tokushima, and salivary cortisol is measured at the Center for Environmental Risk Research, National Institute for Environmental Studies (Supplement 12). The total IgE antibody titer and the specific IgE antibody titers are measured by the ImmunoCAP method provided by health insurance.

## 6.2 ASSESSMENT DETAILS

Study physicians investigate patient information from medical information as listed below. The PACI Study does not examine genetic features of participants.

(1) Study entry

Informed consent, birthday, sex, inclusion criteria, and exclusion criteria

Patient background: gestational age, body weight at birth, body height at birth, past medical history, race

Mother’s background: age at study entry, socioeconomic status (education), history of allergic diseases

Father’s background: socioeconomic status (education), history of allergic diseases

Siblings’ background: number of siblings, history of allergic diseases

Life style: pet ownership at home (dog, cat, and so forth), exposure to second-hand smoke

Nutrition: breastfeeding, milk formula, hypo-allergenic milk formula, solid food introduction, egg, cow’s milk, wheat, soy, and peanut intake, food restrictions during pregnancy and lactation

Body weight at study entry, body height at study entry

History of IgE-mediated FA by interview, history of wheeze by interview

Serum tests: total IgE antibodies titer in serum; egg white titer; ovomucoid, milk, soy, wheat, peanut and Ara h2-specific IgE antibody levels in serum; egg white titer; ovomucoid, milk, soy, wheat, peanut and Ara h2-specific IgG4 antibody levels in serum

Severity of AD: POEM, EASI by blinded physician

QoL: IDQoL and DFI

Concomitant medication/treatment

(2) Week 2, Week 4, Week 8

Life style: pet ownership at home (dog, cat, and so forth), exposure to second-hand smoke

Nutrition: breastfeeding, milk formula, hypo-allergenic milk formula, solid food introduction, egg, cow’s milk, wheat, soy, and peanut intake, food restrictions during pregnancy and lactation,

Body weight

History of IgE-mediated FA by interview, history of wheeze by interview

Severity of AD: POEM, EASI by blinded physician

AD disease-free days, Prescription volume/remaining amount/days used of emollients and TCS used including rescue medication used

Salivary cortisol, concomitant medication/treatment, adverse events

(3) 28 weeks of age

Life style: pet ownership at home (dog, cat, and so forth), exposure to second-hand smoke

Nutrition: breastfeeding, milk formula, hypo-allergenic milk formula, solid food introduction, egg, cow’s milk, wheat, soy, and peanut intake, food restrictions during lactation,

Body weight at study entry, body height at study entry

Food challenge test (hen’s egg): open method investigated by blinded physician at the age of 28 weeks. Pasteurized low egg powder 2.6 g (whole egg 10.4 g, egg protein 1.2 g) is given. Participants eat 0.1–0.5–2 g of the pasteurized egg powder every 40 minutes.

History of IgE-mediated FA by interview, history of wheeze by interview

Serum test: total IgE antibodies titer in serum; egg white titer; ovomucoid, milk, soy, wheat, peanut and Ara h2-specific IgE antibody levels in serum; egg white titer; ovomucoid, milk, soy, wheat, peanut and Ara h2-specific IgG4 antibody levels in serum

Severity of AD: POEM, EASI by blinded physician

AD disease-free days, Prescription volume/remaining amount/days used of emollients and TCS used including rescue medication used

Salivary cortisol, concomitant medication/treatment, adverse events

# 7 ADVERSE EVENTS

Adverse events are defined as any unfavorable symptoms and signs (including anomalies in laboratory test values) occurring in participants, with or without a causal relationship with interventional treatment. When an adverse event develops, study physicians promptly carry out necessary action (examination, treatment, discontinuation of study treatment, and so forth) and make an effort to ensure participant safety.

Study physicians check latest insert on the website of the Pharmaceuticals and Medical Devices Agency <http://www.info.pmda.go.jp/>. An adverse event to be evaluated is recorded in the medical record and electronic case report (eCRF).

## 7.1 COLLECTION OF ADVERSE EVENTS

In this study, we evaluate the following adverse events that occurred from the start of the study treatment to the completion or discontinuation of the study treatment. Adverse drug reactions are defined as any adverse events that cannot be denied relatedness to the study drugs (Hirudoid^®^ Soft ointment, Almeta^®^, Rinderon^®^-V, and Fulumeta^®^). Well-known adverse drug reactions are any events listed in the package inserts. Unknown adverse drug reactions are any events not listed on the package inserts.

(1) serious adverse events (SAEs) (It does not matter whether or not the events are related to the study treatment)

(2) well-known and unknown adverse drug reactions that occur in the study intervention would include those for Hirudoid^®^ Soft ointment, Almeta^®^, Rinderon^®^-V, and Fulmeta^®^

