
SAFETY OF TOPICAL CORTICOSTEROIDS

TCSs are topical anti-inflammatory agents and they are safer than systemic steroids administered via an oral or intravenous route. Absorption of TCS in the skin is considered to depend on many factors such as molecular weight of TCS, cream or ointment bases, application amount, potency of TCS, application period, and age. Cutaneous side effects include telangiectasias, skin atrophy, skin striae, focal hypertrichosis, acne-like eruptions, rosacea-like eruptions, folliculitis, and so forth (24, 25). In an observational study in the US, children with moderate or severe AD did not show adrenal suppression although they had used TCSs for more than several years since infancy (26). Fukuie *et al.* performed rapid ACTH stimulation tests for eight children in the proactive group and four children in the reactive group at 3 months after starting the study intervention and found that no children showed adrenal suppression (21). However, Hanifin *et al.* demonstrated that 2/44 children in the proactive group had adrenal suppression in the RCT (20). Children are more susceptible to steroids than adults and, therefore, their treatment should be carefully considered.

Table 1. TCS potency categories in Japan (1)

| Potency | Generic name and strength | Brand name |
| --- | --- | --- |
| Strongest | 0.05% Clobetasol propionate | Dermovate^®^ |
|  | 0.05% Diflorasone diacetate | Diflal^®^, Diacort^®^ |
| Very strong | 0.1% Mometasone furoate | Flumeta^®^ |
|  | 0.05% Betamethasone butyrate propionate | Antebate^®^ |
|  | 0.05% Fluocinonide | Topsym^®^ |
|  | 0.064% Betamethasone dipropionate | Rinderon^®^-DP |
|  | 0.05% Difluprednate | Myser^®^ |
|  | 0.1% Amcinonide | Visderm^®^ |
|  | 0.1% Diflucortolone valerate | Texmeten^®^, Nerisona^®^ |
|  | 0.1% Hydrocortisone butyrate propionate | Pandel^®^ |
| Strong | 0.3% Deprodone propionate | Eclar^®^ |
|  | 0.1% Dexamethasone propionate | Methaderm^®^ |
|  | 0.12% Dexamethasone valerate | Voalla, Zalucs^®^ |
|  | 0.1% Halcinonide | Adcortin^®^ |
|  | 0.12% Betamethasone valerate | Betnevate^®^, Rinderon^®^-V |
|  | 0.025% Fluocinolone acetonide | Flucort^®^ |
| Medium | 0.3% Prednisolone valerate acetate | Lidomex^®^ |
|  | 0.1% Triamcinolone acetonide | Ledercort^®^ |
|  | 0.1% Alclometasone dipropionate | Almeta^®^ |
|  | 0.05% Clobetasone butyrate | Kindavate^®^ |
|  | 0.1% Hydrocortisone butyrate | Locoid^®^ |
| Weak | 0.1% Dexamethasone | Glymesason^®^, Eurason^®^ |

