## 5.4 BLINDING

Participants, parents, and investigators who treat participants with AD are not blinded to the study intervention. The physicians who perform OFC and examine the skin are blinded to the group allocations. Those who are blinded to the study intervention are required to meet the following criteria.

1. Blinded physicians are not the physicians who treat participants in the PACI Study.
2. Blinded physicians do not look at documents and all other information about the study intervention.

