## 7.2 ASSESSMENT OF ADVERSE EVENTS

Investigators collect and assess adverse events by medical interview, physical examination, and skin diary every study visit. Study physicians assess whether or not participants have adverse drug reactions related to the study drugs. If SAEs and adverse drug reactions are discovered, study physicians record as listed below.

They record diagnosis or event, the day of occurrence, the severity (mild, moderate, or severe), the seriousness (serious or non-serious), the status of the study (continuation, extension, cessation, or stop), the procedure for adverse events (done or not, details if it occurs), the outcome of adverse events (resolved, improved, still present, improved with sequelae, death, unknown, reason if the evaluation is finished with unknown status), the day the physician assesses the status, and relatedness to the study (relatedness denied or relatedness that cannot be denied, evidence of judgment if it is relatedness that cannot be denied).

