## 7.3 REPORTING OF ADVERSE EVENTS

Both SAEs that are considered to be related to the study intervention and SAEs that are considered to be unrelated to the study intervention will be reported to the Pharmaceuticals and Medical Devices Safety Information Reporting System [Article 68 of the Pharmaceutical Affairs Law as applied under Article 10(2)]. Principal study investigator reports to the Minister of Health, Labor and Welfare if a serious adverse event is unpredictable and the direct relatedness to the study cannot be denied. In addition, study physicians report spontaneously to the manufacturer in accordance with the provisions of each research implementation facility for the purpose of cooperating with the manufacturer 's voluntary report [Article 68 of the Pharmaceutical Affairs Law as applied under Article 10(1)]. Investigators will input the SAE and adverse drug reaction information into the medical chart and the eCRF.

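### Non-serious events are recorded only if an unblinded physician does not deny drug relatedness, so the arm comparison of mild cutaneous steroid effects can be distorted in either direction

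*Protocol*

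**What the plan says.** Section 7 of the protocol defines adverse events broadly, irrespective of cause. It then restricts what is written down: "An adverse event to be evaluated is recorded in the medical record and electronic case report (eCRF". Section 7.1 names the events to be evaluated. The first class is "serious adverse events (SAEs) (It does not matter whether or not the events are related to the study treatment". The second is adverse drug reactions, where "Adverse drug reactions are defined as any adverse events that cannot be denied relatedness to the study drugs".

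Recording follows the same two classes. In 7.2: "If SAEs and adverse drug reactions are discovered, study physicians record as listed below". In 7.3: "Investigators will input the SAE and adverse drug reaction information into the medical chart and the eCRF". Section 7.3.2 adds routine eCRF reporting but does not widen the classes, and the adverse-event row in the 6.1 schedule does not either.

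On who decides, 7.2 states: "Study physicians assess whether or not participants have adverse drug reactions related to the study drugs". Under 5.2 the study physician sees the assignment and delivers the treatment, and 5.4 says that "investigators who treat participants with AD are not blinded to the study intervention". The blinded physicians in 5.4 perform the oral food challenge and examine the skin; no section gives them a role in adverse events.

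The two-category relatedness rule in 7.2.4, with its duty to give a reason when an event is called unrelated, is introduced for SAEs only.

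Section 8.2 lists adverse drug reactions as a safety endpoint, alongside SAEs, salivary cortisol, and weight and height. Section 1.1.3 names the local effects of interest: "Cutaneous side effects include telangiectasias, skin atrophy, skin striae, focal hypertrichosis", followed by acne-type and rosacea-type eruptions and folliculitis.

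**The concern.** Events are looked for at every visit by interview, examination and diary (7.2), but a non-serious event that the study physician considers unrelated need not reach the eCRF. The physician making that call knows which infants receive steroid on a schedule (5.6.3) and which receive it only for rash (5.6.4). The same folliculitis could more readily be linked to treatment in the aggressive arm. A physician who favours the proactive regimen could do the reverse. The direction is not predictable.

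At stake is one secondary safety endpoint and, through 9.3.4, part of what the data monitoring committee sees at the interim analysis. Because the restriction acts at data collection, an SAP cannot restore a mild sign that was never entered. The protocol itself describes children as more susceptible to steroids than adults (1.1.3), so local tolerability is a question it should be able to answer fairly.

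**Working it through.** The protocol gives no expected rate or power for adverse drug reactions, so there is no figure to reproduce. The check is textual first, then an illustration.

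**1. Path of a non-serious event.** It is detected at a visit (7.2). The study physician, who knows the allocation (5.2, 5.4), judges relatedness (7.2). If relatedness is not denied, the event is an adverse drug reaction (7.1) and is entered (7, 7.2, 7.3). If it is denied, no section requires entry, and the requirement in 7.2.4 to record a reason is written for SAEs.

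**2. Which safety endpoints in 8.2 depend on that judgement.**

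| Endpoint | Depends on attribution? |
| --- | --- |
| SAEs | No (7.1) |
| Salivary cortisol | No, measured |
| Weight and height | No, measured |
| Non-serious adverse drug reactions | Yes |

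Skin infections treated with antibiotic, antiviral or antifungal ointment are partly traceable, because concomitant therapy is collected at every visit (5.7, 6.1). Untreated atrophy, telangiectasia or striae have no such trace.

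**3. Formula.** Let t be the true event rate in an arm and a the probability that relatedness is not denied. The recorded rate is t × a, so

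recorded ratio = (true rate ratio) × (a aggressive ÷ a conventional).

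**4. No true difference (assumed rates).** With t = 10% in both arms and a = 80% versus 60%:
- recorded rates: 0.10 × 0.80 = 8% and 0.10 × 0.60 = 6%; ratio 8 ÷ 6 = 1.33
- expected counts with 325 per arm (5.1.3): 325 × 0.08 = 26.0 and 325 × 0.06 = 19.5
- chance of p < 0.05 (two-sided pooled z-test): the pooled rate is 7%, the null standard error √(0.07 × 0.93 × 2 ÷ 325) = 0.0200, and the alternative standard error √((0.08 × 0.92 + 0.06 × 0.94) ÷ 325) = 0.0200. Then Φ((0.02 − 1.96 × 0.0200) ÷ 0.0200) ≈ 0.17; the other tail is negligible.

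Range over assumed values (recorded rates, then chance of p < 0.05):

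| True rate, both arms | 80% v 60% (ratio 1.33) | 90% v 50% (ratio 1.8) | 90% v 30% (ratio 3.0) |
| --- | --- | --- | --- |
| 5% | 4.0% v 3.0%; 11% | 4.5% v 2.5%; 28% | 4.5% v 1.5%; 61% |
| 10% | 8% v 6%; 17% | 9% v 5%; 52% | 9% v 3%; 90% |
| 20% | 16% v 12%; 31% | 18% v 10%; 84% | 18% v 6%; >99% |

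With equal attribution the chance is the nominal 5%.

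**5. The reverse direction (assumed).** A true 10% v 5% with attribution 60% v 80% records 0.10 × 0.60 = 6% v 0.05 × 0.80 = 4%, so a true ratio of 2 appears as 1.5.

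**6. After the fix.** If listed signs are recorded whatever their relatedness, a = 1 in both arms and the recorded ratio equals the true ratio as far as attribution is concerned. Differential detection or parental reporting is untouched.

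**The case against.** The filter is inclusive: an event is kept unless relatedness can be denied, so doubtful cases should go in. Relatedness covers four study drugs. The emollient is applied twice daily in both arms, and the conventional arm uses the same steroids on rash, so a study drug is often a possible cause in either arm. Package inserts, which physicians are told to consult, give a reference list that is neutral between arms. Restricting collection in this way is explicit and consistent across section 7, and 15.1 places the drugs within daily clinical practice. It is a design choice, not a contradiction. All of this stands, and it limits differential attribution without removing it.

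A reader might infer three stronger things that the protocol does not support:
- **That the safety or benefit-risk assessment as a whole is compromised.** SAEs, cortisol and growth do not depend on attribution, and they cover serious, adrenal and growth effects.
- **That every unrecorded event is lost.** Treated skin infections can partly be found through concomitant therapy.
- **That a doubling is to be expected.** A ratio of 2 with no true difference needs something like 80% versus 40% attribution, that is, relatedness denied for 60% of conventional-arm events. Nothing in the protocol supports that, and it fits poorly with the inclusive threshold.

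It is also fair to object that sending the blinded skin examiner to look for steroid signs could suggest the allocation. That would put EASI at risk and, if the same physician scores the food challenge, the primary endpoint too. This stands and shapes the fix.

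**Conclusion.** The concern holds in a limited form. Entry of non-serious events depends on an unblinded judgement that has no stated criterion outside SAEs and leaves no required record when relatedness is denied. The between-arm comparison of non-serious adverse drug reactions, chiefly mild cutaneous steroid effects, can therefore be inflated or diluted by differential attribution.

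The documents do not show that such a difference will occur, and they fix neither its size nor its direction. Every rate in the illustration is an assumption. The mildest gap examined (80% v 60%) gives a ratio of 1.33 and, for true rates of 5% to 20%, an 11% to 31% chance of a nominally significant difference where none exists. This is a cheap improvement to one secondary safety endpoint. It does not affect the primary analysis.

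**What to change.** In 7.1, 7.2 and the eCRF, add a short fixed list: the cutaneous effects named in 1.1.3, plus skin infections. Record each as present or absent in both arms at visits 2 to 5, regardless of relatedness, and keep relatedness as a descriptive field. Compare the arms on this list and show physician-attributed reactions as a secondary display.

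The study physician can complete it during the examination that 7.2 already requires. If the blinded skin examiner is used instead, the list should be completed after EASI is scored, and not by the physician who scores the food challenge.

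The cost is slightly more data entry, with no new visit or procedure. Some detection bias remains if the assessor is unblinded, and there is some unblinding risk if the blinded examiner is used. The protocol should state which of the two it accepts.
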